## Abstract

**Background:**

Thrice-weekly haemodialysis is the usual dose when starting renal replacement therapy; however, this schedule is no longer appropriate since it does not consider residual renal function. Several reports have suggested the potential benefit of beginning haemodialysis less frequently and incrementally increasing the dose as the residual renal function decreases. However, all the data published so far are from observational studies. Thus, this clinical trial avoids any potential selection bias and will assess the possible benefits that have been observed in observational studies.

**Methods/design:**

This report describes the study protocol of a randomized prospective multi-centre open-label clinical trial to evaluate whether starting renal replacement therapy with twice-weekly haemodialysis sessions preserves residual renal function better than the standard thrice-weekly regimen. We also explore other clinical parameters, such as concentrations of uremic toxins, dialysis doses, control of anaemia, removal of medium-weight uremic toxins, nutritional status, quality of life, hospital admissions and mortality. Only incident haemodialysis patients who can maintain a urea clearance rate KrU ≥ 2.5 mL/min/1.73 m^2^ are eligible. Patient recruitment began on 1 January 2017 and will last for 2 years or until the required sample size has been recruited to ensure the established statistical power has been reached. The minimum follow-up period will be 1 year. Anuric patients with acute renal failure and patients who return to haemodialysis after a kidney transplant failure are excluded. It has been calculated that 44 patients should be recruited into each group to achieve a power of 80% in a two-sided comparison of means with a usual significance level of 0.05. A time-to-event analysis will estimate the probability of kidney function survival in both groups using the Kaplan–Meier method. Survival curves will be compared with log-rank tests. This survival analysis will be complemented with a proportional hazard model to estimate the hazard ratio of kidney function survival adjusted for any confounding factors. Analyses will be carried out in accordance with the intention-to-treat principle.

**Discussion:**

The incremental initiation of dialysis may preserve residual renal function better than the conventional treatment, with similar or higher survival rates, as reported by observational studies. To our knowledge, this is the first clinical trial to evaluate whether initiating renal replacement therapy with twice-weekly haemodialysis sessions preserves residual renal function better than beginning with the standard thrice-weekly regimen.

**Trial registration:**

ClinicalTrials.gov, NCT03302546. Registered on 5 October 2017.

## Background

The usual schedule is thrice-weekly haemodialysis sessions, and only a few patients receive dialysis less frequently [1]. Data from Spain indicate that whereas 8% of patients are dialysed more often than 3 days per week, only 1% do so at a lower frequency [1]. Based on model of urea kinetics, Gotch and Keen [2] proposed that an adequate dose of dialysis could be achieved with two dialysis sessions per week, as long as the residual urea clearance rate KrU ≥ 2.5 mL/min/1.73 m^2^. However, adherence to this scheme is low, based on data in the Dialysis Outcomes Practice Patterns Study [1] and on clinical guides, like the 2015 Kidney Disease Outcomes Quality Initiative (KDOQI) guidelines [3].

Periodically measuring the renal urea clearance rate is not common practice in haemodialysis units because renal function is considered to decrease rapidly after the onset of dialysis treatment. This could, in part, justify the poor implementation of lower-frequency haemodialysis. However, in recent years there has been growing interest in less frequent dialysis schemes [1, 4–8], though this is not without significant controversy [9–11].

Beginning haemodialysis less frequently and incrementally increasing the dose as residual renal function decreases is referred to as incremental or progressive haemodialysis [4–7, 11]. Most of the published works highlight that incremental haemodialysis may preserve residual kidney function [4–7], which has significant relevance for haemodialysis treatment [8, 12, 13]. Maintaining residual kidney function, other than allowing more liquid intake, contributes to a greater elimination of medium-sized molecules and has beneficial effects on anaemia, inflammation, and high blood pressure [8, 12–15]. The preservation of residual renal function is one of the adequacy goals of haemodialysis treatment in the KDOQI guidelines [3]. Moreover, incremental haemodialysis is associated with lower doses of erythropoietin [4, 7], better nutritional status [15, 16], lower concentrations of beta-2 microglobulin [7, 17], lower volume overload [7, 18], better quality of life [13], lower rate of hospital admissions [14, 19] and survival rates equal to or greater than those achieved with the conventional three-sessions per week scheme [7, 12, 16, 18–20].

The Haemodialysis Unit of the Nephrology Department of Hospital Universitario Ramón y Cajal is a pioneer in implementing an incremental haemodialysis program, having more than 10 years of experience [4, 5, 7, 17]. Our incremental program is based on the models of Gotch and Keen [2]. It uses a threshold of 2.5 mL/min/1.73 m^2^ to indicate when to increase the frequency of haemodialysis. This program has had satisfactory results and no clinical side effects in our previous experience [4, 5, 7, 17].

The percentage of patients who start renal replacement treatment with two weekly sessions has increased from 28% in 2006 to 84% in 2017. Currently, about 25% of the patients in our unit are treated with this twice-weekly frequency [17]. We have observed beneficial effects on the management of anaemia and hospitalization rates [3, 7], a lower concentration of beta-2 microglobulin (which is a marker of medium-sized molecules [7]) and no volume overload, as measured by bioimpedance [7]. The maintenance of residual renal function is similar among patients who start with an incremental haemodialysis regimen and those who begin peritoneal dialysis [5].

However, note that published studies on incremental haemodialysis are observational, with potential selection bias [4–7, 12, 15, 18]. In addition to differences in renal function at the start of haemodialysis, some centres exclude patients with certain comorbidities [11]. Thus, this clinical trial avoids selection bias and will assess the possible benefits that have been observed in observational studies.

To our knowledge, this is the first clinical trial to evaluate whether initiating renal replacement therapy with twice-weekly haemodialysis sessions preserves residual renal function better than beginning with the standard thrice-weekly regimen. Recently, the study protocol has been published of another clinical trial that assesses whether incrementally starting with one session of haemodialysis per week reduces mortality in incident patients compared with patients who start renal replacement therapy with the conventional method [21].

## Methods/design

### Hypothesis

Our hypothesis is that initiating renal replacement therapy with twice-weekly haemodialysis sessions preserves residual renal function better than the conventional regimen of beginning with thrice-weekly sessions. In addition, we hypothesise that maintaining renal function provides beneficial clinical effects, such as better control of anaemia, greater removal of medium-weight uremic toxins, and better nutritional status and quality of life, and has a safety profile like that of the conventional schedule.

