### Outcomes

The main outcome is loss of kidney function, defined as urine volume output less than 100 mL in 24 h, 12 months after the initiation of haemodialysis therapy.

The secondary outcomes are: (1) erythropoietin dosage, (2) beta-2 microglobulin concentration, (3) hydration and nutritional status, (4) concentrations of uremic toxins, (5) dialysis dose, (6) number and duration of hospital admissions, (7) mortality and (8) quality of life.

In addition, cost-efficiency will be assessed by recording the cost of haemodialysis sessions and the monthly consumption of erythropoietin.

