### Sample size

Considering the data published in observational studies [4, 5, 7] and assuming an average decrease in the glomerular filtration rate of 0.18 mL/min/month in the 2HD group and 0.33 mL/min/month in the 2HD group [7], with a standard deviation of 0.25, 44 patients should be recruited into each group to achieve a power of 80% in a two sided comparison of means with a usual significance level of 0.05.

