### Data collection and statistical analysis

The data collected will be stored in a database specially designed for this study using Access (Microsoft Office Access 2007). The data will be entered by a dedicated member of the project team, who will ensure the integrity and quality of the data. The statistical analyses will be carried out with the statistics program Stata v.14 [25].

We will perform a blind interim analysis when at least half of the patients have been recruited and followed for at least 1 year. We will stop the trial if the group difference in the main outcome is statistically significant at a significance boundary *p* < 0.0051. The final analysis with the whole trial population will be carried out at the end of the follow-up at a significance level of 0.04795.

For the univariate analysis of quantitative variables, we will check the normality of the data using the Kolmogorov–Smirnov test. Depending on the assumption of normality, the two arms will be compared using parametric tests (Student’s *t*-test) or nonparametric tests (Mann–Whitney *U* test). The associations of categorical variables with the two treatment groups will be assessed by chi-squared tests or Fisher exact tests, as appropriate.

The loss of renal function is evaluated by the diuresis in 24 h at 12 months after initiation of haemodialysis therapy, and it is dichotomized with a threshold of 100 mL in 24 h. A time-to-event analysis will estimate the probability of loss of kidney function in both treatment groups using the Kaplan–Meier method. Survival curves will be compared with log-rank tests. This survival analysis will be complemented with a proportional hazard model to estimate the hazard ratio of kidney function survival adjusted for any confounding factors to identify any imbalance in the baseline characteristics of the patients.

All analyses will be carried out in accordance with the intention-to-treat and per-protocol principles, assuming that in the worst case the losses to follow-up are a failure of the allocated treatment arm. In the final analyses, for the comparisons between the two treatment groups, the probability of rejecting the null hypothesis will be adjusted according to the O’Brien and Fleming method [26].

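### The safety hypothesis claims similarity, but the stated tests look only for a difference and 44 patients per arm cannot support the claim

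*Protocol article*

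**What the plan says.** **Hypothesis.** The second sentence closes with the expectation that the approach "has a safety profile like that of the conventional schedule". Its grammatical subject is the maintenance of renal function, but a comparison with the conventional schedule makes sense only for the twice-weekly start (2HD).

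**Outcomes.** The secondary outcomes that bear on safety include "number and duration of hospital admissions" and mortality. None is named as the safety endpoint and no margin is attached to any. Separately, "cost-efficiency will be assessed by recording the cost of haemodialysis sessions and the monthly consumption of erythropoietin".

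**Data collection and statistical analysis.** For quantitative variables: "Depending on the assumption of normality, the two arms will be compared using parametric tests" (Student's t), with Mann-Whitney as the alternative. For categorical variables: "The associations of categorical variables with the two treatment groups will be assessed by chi-squared tests or Fisher exact tests, as appropriate". The Kaplan-Meier, log-rank and proportional hazards methods are tied to loss of kidney function.

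**Sample size.** "44 patients should be recruited into each group to achieve a power of 80% in a two sided comparison of means". The means are monthly declines in glomerular filtration rate.

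**Follow-up.** Participants and Recruitment period set a minimum of one year. Withdrawal criteria end a patient's follow-up at transplant, death, recovery, transfer or withdrawal of consent. Assessments records admissions, days of admission and their causes every two months.

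The Discussion adds that establishing the safety of incremental haemodialysis is essential.

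**The concern.** A hypothesis of similarity needs either an interval judged against a margin or a plain statement that the aim is to estimate. A test for a difference gives neither: failing to reject equality is what a small trial produces both when the arms are alike and when they differ by an amount it cannot see. The article pairs a similarity hypothesis with difference tests and a sample size chosen for another quantity, so the stated analysis cannot answer the stated question.

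Two further features weaken the safety and cost comparison. Admissions accrue over time, and time under observation differs between patients and can be cut short by death. The general t-test or Mann-Whitney rule contains nothing that corrects for this. And the cost comparison counts two items on which the Discussion expects 2HD to come out lower, sessions and erythropoietin. It leaves out hospital stays, where any harm from less dialysis could appear as cost.

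**Working it through.** **1. The plan's own figure.** Inputs from Sample size: declines of 0.18 and 0.33 mL/min/month (both printed as 2HD; the second is read as 3HD), SD 0.25, two-sided 0.05, power 80%.

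n per arm = 2 × (1.960 + 0.842)² × (0.25 / 0.15)² = 43.6, rounded up to 44. The figure reproduces, and it concerns filtration rate only.

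**2. Precision for mortality with 44 per arm.** The article gives no event rate, so the one-year risks p below are assumptions. Half-width of the 95% interval when both arms have risk p: 1.96 × √(2p(1−p)/44).

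| Assumed risk | Calculation | Half-width |
|---|---|---|
| 5% | 1.96 × √(0.095/44) | 9.1 points |
| 10% | 1.96 × √(0.18/44) | 12.5 points |
| 20% | 1.96 × √(0.32/44) | 16.7 points |

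**3. Power to see a doubling.** Exact power of the chi-squared test at the article's final level of 0.04795, summing binomial probabilities over all significant 2 × 2 tables. Fisher's test, the article's alternative, is shown at 0.05.

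| Risks compared | Chi-squared | Fisher |
|---|---|---|
| 5% and 10% | 13% | 5% |
| 10% and 20% | 26.5% | 17% |
| 20% and 40% | 54% | 45% |

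Hand check for 10% against 20% (normal approximation, level 0.05): the pooled standard error is √(2 × 0.15 × 0.85/44) = 0.0761 and the standard error under the alternative is √((0.09 + 0.16)/44) = 0.0754. Then (0.10 − 1.96 × 0.0761)/0.0754 = −0.65, which gives power of about 26%.

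**4. What a margin would need.** n per arm = (1.960 + 0.842)² × 2p(1−p)/margin², one-sided 0.025, equal true risks. For an illustrative 10-point margin this is 75, 142 and 252 per arm at 5%, 10% and 20% risk. With 44 per arm the power is 58%, 35% and 22%. For a 20-point margin it is 99%, 88% and 65%.

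**5. Admissions as rates.** With one year per patient and an assumed rate r per patient-year, the 95% interval for a rate ratio near 1 spans a factor of exp(1.96 × √(2(1/r + k)/44)) either way, where k is overdispersion. For r from 0.5 to 1.0, the factor is 1.8 to 1.5 with k = 0, and 2.1 to 1.8 with k = 1. Power for a rate ratio of 1.5 is 21% to 55% across these cases.

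**6. Admissions as counts.** Illustration with an assumed true rate of 1.0 per patient-year in both arms, one-year mortality of 10% and 20%, and deaths spread evenly over the year. Mean time observed is 1 − 0.10/2 = 0.95 and 1 − 0.20/2 = 0.90 years. Expected admissions per patient are then 0.95 and 0.90. The arm with twice the deaths shows about 5% fewer admissions (0.90/0.95 = 0.947) although the rates are equal. The distortion is modest here and grows if deaths fall earlier in the year.

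**The case against.** - **A reader might infer that the plan will treat a non-significant safety test as proof of similar safety, or will conclude that 2HD is equally safe and cheaper.** The article says neither. It attaches no decision rule to any safety comparison, and the Discussion presents safety as a question still open. This objection stands: the defect is that the hypothesis and the methods do not fit together, not that a false conclusion is planned.
- **A reader might infer that safety rests on raw admission counts.** It does not: mortality and duration of admission are also outcomes. Nor does the article say that exposure will be ignored. A rate per patient-year is also a quantitative variable, and the Background speaks of hospitalization in terms of rates. So the point on admissions holds only if counts are entered as they are.
- **Staggered entry should balance between arms**, since randomization is 1:1 within centres, and quality of life closes at 12 months. This stands too. Bias needs follow-up to end differently in the two arms, and in the illustration above it is small.
- **Low power for a secondary safety outcome is ordinary in a superiority trial of this size, and the event rates are assumed.** Both are true. Low power becomes a fault of the plan only when it is paired with a hypothesis of similarity.
- **An analysis plan that is not shown could hold a margin or a rate model.** It could, but it would have to add to or depart from the tests that the article fixes.
- **Cost is an additional assessment outside the numbered outcomes, and its scope is a design choice.** That limits its weight. The omission remains, because the admission data are collected.

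**Conclusion.** The point holds as a mismatch on a secondary objective. The article hypothesises similar safety, names only difference tests, gives no criterion for similarity and sizes the trial on filtration rate alone. At assumed one-year mortality of 5% to 20%, the interval for a risk difference near zero is about ±9 to ±17 points, and a doubling would be detected about 13% to 54% of the time. Non-significance would thus be compatible with substantial harm and could not support *like*. The range depends on the assumed risks, but across all of it a doubling is missed in nearly half of trials or more.

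The exposure point is conditional on how admissions are entered, and the cost point is an omission of recorded data. Neither affects the primary comparison.

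**What to change.** - **Hypothesis:** reword the safety part as descriptive, with the aim of estimating differences in mortality and admissions between arms. Alternatively, name the safety outcome and judge its interval against a margin that the investigators set and justify in advance. Unless that margin is wide, 44 per arm will seldom meet it, so the descriptive wording is the more realistic choice. Interval estimates alone, without one of these two changes, would leave *like* without a criterion.
- **Data collection and statistical analysis:** report mortality as a risk difference or hazard ratio with a 95% confidence interval. Report admissions and hospital days as rate ratios with 95% confidence intervals from a negative binomial model with log follow-up time as offset. Show deaths by arm alongside, because the offset corrects for time observed but not for why observation ended. State that a non-significant result is not evidence of similar safety.
- **Outcomes:** add recorded hospital days times a unit cost to the cost comparison.

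The cost is a few sentences, a little more analysis and a source for the unit cost. No extra patients or clinical data are needed, since admissions and days are already collected. The downside is a more modest safety claim.

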### Outcomes

The main outcome is loss of kidney function, defined as urine volume output less than 100 mL in 24 h, 12 months after the initiation of haemodialysis therapy.

The secondary outcomes are: (1) erythropoietin dosage, (2) beta-2 microglobulin concentration, (3) hydration and nutritional status, (4) concentrations of uremic toxins, (5) dialysis dose, (6) number and duration of hospital admissions, (7) mortality and (8) quality of life.

In addition, cost-efficiency will be assessed by recording the cost of haemodialysis sessions and the monthly consumption of erythropoietin.

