#### Inclusion criteria

Prospective participants must have stage 5 chronic kidney disease, must have started chronic haemodialysis and must be able to maintain a residual urea clearance rate KrU ≥ 2.5 mL/min/1.73 m^2^. Before enrolment, participants must sign the informed consent form.

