### Withdrawal criteria

Patients will be withdrawn from the study if they receive a renal transplant, die***,*** recover renal function or transfer to another facility or if they withdraw their informed consent.

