### Assessments

The following will be assessed at the momento fo enrollment: age, sex, renal disease, Charlson comorbidity index, urine volume output in 24 h (mL), urea clearance (mL/min), creatinine clearance (mL/min).

The following will be assessed at the start of haemodialysis treatment (baseline) and every 2 months during a follow-up of at least 1 year: urine volume output in 24 h (mL), urea clearance (mL/min), creatinine clearance (mL/min), haemoglobin (g/dL), haematocrit (%), creatinine (mg/dL), urea (mg/dL), Na (mmol/L), K (mmol/L), albumin (g/dL), pre-albumin (mg/dL), calcium (mg/dL), phosphorus (mg/dL), parathyroid hormone (pg/mL), ferritin (ng/mL), beta-2 microglobulin (mg/L), brain-derived natriuretic peptide (pg/mL), C-reactive protein (mg/L), dose of dialysis (*Kt / V*), erythropoietin dosage (units per week per kg of weight), hydration, nutrition, hospital admissions, days of admission, causes of hospitalization and number of haemodialysis sessions.

The dose of dialysis is determined using the kinetic model of urea with the formulae modified from Gotch [22]. Dialysis *Kt* / *V* [3] is added to the residual renal function to give the total *Kt* / *V*:

Total *Kt* / *V* = dialysis *Kt* / *V* + (9.5 KrU) / *V* (for 2 haemodialysis sessions per week)

and

Total *Kt* / *V* = dialysis *Kt* / *V* + (5.5 KrU) / *V* (for 3 haemodialysis sessions per week),

where *V* is 58% of the dry weight (Watson formula) [23] and KrU is the residual urea clearance rate (mL/min).

Hydration and nutrition are measured by multi-frequency electrical bioimpedance (BCM®, Fresenius Medical Care). The following metrics are collected: overhydration (L), amount of extracellular water (L), amount of intracellular water (L), extracellular / intracellular ratio, body mass index (kg/m^2^), lean tissue index (kg/m^2^) and fat tissue index (kg/m^2^).

Quality of life will be assessed using the Kidney Disease Quality of Life Short Form at the start of haemodialysis treatment (baseline), at 6 months and at 12 months (close-out). This is a validated questionnaire for the haemodialysis population.

The schedule of enrolment, intervention and assessments is shown in Fig. 1.

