## Discussion

The transition from pre-dialysis to renal replacement therapy is a crucial moment for patients with chronic renal failure and has significant clinical, social and occupational impacts [27]. Although dialysis therapy may predispose someone to losing their residual renal function, a significant proportion of dialysis patients maintain some degree of renal function long after the initiation of dialysis. In addition, maintaining the residual function may have a positive impact on the survival of haemodialysis patients [8, 12–15].

An incremental approach to the initiation of dialysis may allow some patients to retain more of their residual renal function with an improved quality of life and similar or higher survival rates than those receiving the conventional treatment, as reported by observational studies [4–7, 12, 16, 18, 19, 28]. We also consider that the incremental schedule facilitates the transition to renal replacement therapy and additionally, contributes to reducing health-care costs, not only because there are fewer haemodialysis sessions but also a lower consumption of erythropoietin [4, 7].

However, all previous studies have been observational, and prospective trials, such as this one, are required to determine, without selection bias, the potential benefits and safety of the incremental schedule [9–11, 28], and to establish the optimal group of patients who would benefit from this therapy.

This randomized clinical trial compares twice- versus thrice-weekly haemodialysis sessions for patients who can maintain a residual urea clearance rate KrU ≥ 2.5 mL/min/1.73 m^2^, without excluding a priori patients with severe comorbidities. In our experience, more than 80% of patients who started incremental renal replacement treatment did not suffer from any relevant complications [17]. For these patients, the dose of dialysis was progressively adjusted as their residual renal function declined. In our protocol, diuresis in 24 h is used as a proxy of residual renal function. The transition to more frequent treatment sessions occurs once residual renal function starts to decrease. However, it is essential to determine whether incremental haemodialysis is a safe form of dialysis treatment.

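### The hypothesis and the sample size concern decline in residual renal function, but the outcome list measures it directly only as urine below 100 mL/24 h; clearance, already collected every 2 months, should be a named secondary outcome

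*Protocol article*

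**What the plan says.** All references are to the Protocol article.

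- **Hypothesis:** "initiating renal replacement therapy with twice-weekly haemodialysis sessions preserves residual renal function better than the conventional regimen".
- **Sample size:** 44 per group for a two-sided comparison of means, "assuming an average decrease in the glomerular filtration rate of 0.18 mL/min/month in the 2HD group" and 0.33 in the other group, SD 0.25, 80% power, significance level 0.05. The text labels both rates 2HD; the second is read here as 3HD.
- **Outcomes, main:** "The main outcome is loss of kidney function, defined as urine volume output less than 100 mL in 24 h", at 12 months.
- **Outcomes, secondary:** "The secondary outcomes are: (1) erythropoietin dosage, (2) beta-2 microglobulin concentration, (3) hydration and nutritional status, (4) concentrations of uremic toxins, (5) dialysis dose", followed by hospital admissions, mortality and quality of life. A cost assessment is added. Neither KrU, creatinine clearance nor GFR decline appears.
- **Assessments:** measured at baseline and "every 2 months during a follow-up of at least 1 year: urine volume output in 24 h (mL), urea clearance (mL/min"; creatinine clearance is next in the same list.
- **Data collection and statistical analysis:** Kaplan-Meier, log-rank and proportional hazards for the dichotomised diuresis. Separately, quantitative variables are compared between arms by t-test or Mann-Whitney test, with no adjustment mentioned.
- **Discussion:** "In our protocol, diuresis in 24 h is used as a proxy of residual renal function".

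**The concern.** The quantity that the hypothesis names, and on which the trial was sized, is not among its declared outcomes. Anuria is a late, yes/no reading of that quantity. If few patients become anuric by month 12, or the arms do not differ, no declared outcome can show whether clearance itself was preserved. If anuria does differ, no declared outcome shows whether clearance agrees with the proxy.

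The listed outcomes that touch on kidney function do not fill the gap. KrU enters total Kt/V only as an added term whose multiplier depends on the schedule (9.5 for two sessions, 5.5 for three). At the same KrU of 2.5 that term is 9.5 × 2.5 / V = 23.75 / V in one arm and 5.5 × 2.5 / V = 13.75 / V in the other. A difference in total Kt/V can therefore arise with identical kidney function. Beta-2 microglobulin and uremic toxins also depend on removal by dialysis.

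**Working it through.** **1. What the 44 per group is for.** Inputs from Sample size: difference 0.33 − 0.18 = 0.15, SD 0.25, two-sided 0.05, power 80%.

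n = 2 × (1.960 + 0.842)² × 0.25² / 0.15² = 2 × 7.85 × 2.778 = 43.6, so 44 per group. Power at 44 is 80.4% (79.5% by the t-test). At the final significance level of 0.04795 it is 79.9%. The plan's figure reproduces, and it is a figure for mean decline.

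**2. The same 44 applied to anuria.** The article gives no anuria rates, so these are assumed. Suppose a twice-weekly start halves the 12-month risk (two proportions, two-sided 0.05):

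| Risk on 3HD | 10% | 20% | 30% | 40% | 50% |
|---|---|---|---|---|---|
| Power at 44 per group | 14% | 26% | 39% | 54% | 68% |
| n per group for 80% | 435 | 199 | 121 | 82 | 58 |

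**3. Why entry KrU matters.** Assume that the planning rates apply to KrU and that anuria means KrU 0. Entry requires that patients "must be able to maintain a residual urea clearance rate KrU ≥ 2.5 mL/min/1.73 m^2", and 2HD patients move to three sessions below the same threshold.

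- Average patient entering at 5: after 12 months 5 − 12 × 0.18 = 2.84 on 2HD and 5 − 12 × 0.33 = 1.04 on 3HD. Neither is anuric, yet clearance differs by 1.80 mL/min.
- Average patient entering at 2.5: on 3HD, anuric at 2.5 / 0.33 = 7.6 months. On 2HD the switch comes almost at once. If decline then runs at 0.33, the arms hardly differ on either measure. If 0.18 holds throughout, 2.5 − 2.16 = 0.34 remains at month 12: the arms differ on anuria, but by only 0.34 on KrU because it cannot fall below 0.

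**4. Simulated power.** 6,000 trials of 44 against 44 per scenario. Assumptions not in the article: entry KrU uniform from 2.5 to the stated upper limit; individual slopes normal with SD 0.25; KrU floored at 0; lognormal measurement error with CV 0 or 30%. A 2HD patient switches after two readings below 2.5, half a month apart. Visits are 2-monthly to month 12. Anuria is tested by log-rank, and 12-month KrU by comparison adjusted for baseline. In branch A decline becomes 0.33 after switching. In branch B 0.18 already includes time after switching.

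| Branch, CV | Measure | to 4 | to 5 | to 6 | to 8 |
|---|---|---|---|---|---|
| A, 0 | Anuria | 17.6% | 22.1% | 21.8% | 20.4% |
| A, 0 | KrU | 45.3% | 53.1% | 60.1% | 66.5% |
| A, 30% | Anuria | 21.3% | 23.5% | 23.0% | 21.0% |
| A, 30% | KrU | 37.9% | 44.8% | 49.2% | 52.8% |
| B, 0 | Anuria | 64.6% | 62.0% | 57.1% | 45.3% |
| B, 0 | KrU | 66.4% | 69.0% | 70.2% | 72.7% |
| B, 30% | Anuria | 65.9% | 61.5% | 56.3% | 45.6% |
| B, 30% | KrU | 61.2% | 61.9% | 61.8% | 61.4% |

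The standard error of each figure is at most √(0.25 / 6,000) = 0.65 percentage points, so 61.9% against 61.5% is a tie. With equal slopes, rejection was 5.0-5.6%. If all patients enter at 2.5-3.0: A 27-33% for KrU against 12-18% for anuria; B 58-63% against 67-69%, so anuria is ahead there. With 20% random withdrawals, CV 20% and completers only: A 34-50% against 18-21%; B 54-57% against 39-60%. With gamma slopes, so that clearance never rises, the KrU advantage widens: A 73-92% against 22-31%; B 83-99% against 45-77%.

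**The case against.** **A clearance comparison is not wholly unforeseen.** A reader might infer that any later KrU comparison would be purely post hoc. The article does not support that. Clearance is in the assessment list, the analysis section plans two-arm tests of quantitative variables without limiting them to the numbered outcomes, and the sample size fixes a comparison of mean decline in advance. This stands. What remains is that clearance is undeclared as an outcome, and that the general test does not adjust for baseline.

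**Anuria was a deliberate, disclosed choice.** Limitations defends it as objective in an open-label trial, whereas KrU triggers a treatment change in one arm. This is a good reason to keep anuria as the main outcome. It is no reason to leave clearance off the list, since arms can be compared as randomised whatever the switching. Nor should a reader infer that switching biases the trial: it is part of the strategy under test.

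**The power gain is not robust.** This also stands. The centre's own programme used the same 2.5 rule (Background), so branch B is plausible. If Kaplan-Meier used 12-36 months of follow-up (1,500 trials, CV 0), anuria power would rise to 24-32% in A and 61-69% in B, against 48-66% and 66-74% for 12-month KrU. In the main simulation 12-month KrU never reaches 80%, and it is not the same summary as the monthly decline used for sizing.

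**The article is condensed.** Analysis detail may well lie elsewhere. But the article gives a numbered outcome list that omits the quantity in its own sample-size calculation.

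**Conclusion.** The point holds as a mismatch between the hypothesis and sample size on one side and the declared outcomes on the other. It does not make the main outcome invalid. The 44 per group reproduces exactly for mean clearance decline, and the 80% power should not be read as power for anuria.

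A reader might infer that KrU would certainly be the more powerful outcome. The documents do not support this: they give neither the entry distribution of KrU, nor its measurement error, nor whether 0.18 includes time on three sessions. The advantage is clear in branch A (38-67% against 18-24% over all simulated entry ranges and errors). In branch B it is small or absent when most patients enter near 2.5. The case therefore rests mainly on measuring what the hypothesis names, with data already being collected.

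**What to change.** Keep the main outcome and the switching rule. Add to the secondary outcomes: decline in residual urea clearance (KrU, mL/min/1.73 m²) over 12 months, compared between randomised arms regardless of switching. Use all scheduled 2-monthly values up to withdrawal in a repeated-measures model adjusted for baseline KrU. Set KrU to 0 once a patient is anuric, and report the adjusted difference at 12 months.

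State in Sample size that the 80% power refers to mean clearance decline and not to the anuria outcome.

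State how early exits are handled. "Patients will be withdrawn from the study if they receive a renal transplant", and also on death, recovery of function, transfer or withdrawn consent. These differ in what they imply for KrU, so one imputed value for all would not serve.

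Avoid relying on time to a single KrU reading below 2.5: its power falls from 51-60% without measurement error to 39-43% at CV 30%, and patients entering at about 2.5 would have events almost at once.

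Cost: a few lines in the outcomes and sample size, one more secondary outcome and one more analysis, plus the handling of deaths, transplants and other withdrawals. Care, visits and sample size do not change.
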